## Methods

To our knowledge, SCED has never before been applied to IPV evaluation; therefore, the methods in this study involved developing novel safety protocols for women engaging with high-touch research while at high risk for IPV, as well as data collection and analysis procedures.

### Ethical Considerations

This study and all relevant protocols were reviewed and approved by the St Michael’s Hospital Research Ethics Board (REB; #20‐120). All study procedures comply with the ethical standards of the St Michael’s Hospital REB and follow the principles outlined in the Declaration of Helsinki and relevant Committee on Publication Ethics (COPE) and JMIR guidelines. Further details on informed consent, privacy, and confidentiality are provided in the following sections. Below, we review the development of safety protocols before describing the evaluation of the WITHWomen Pathways app.

### Universal Safety Considerations

In-person interviews will be conducted in complete privacy, except for participants who are accompanied by children younger than 2 years. If privacy cannot be ensured, interviewers will reschedule the interview for a different time or place, allowing participants the flexibility to choose a safer or more convenient option. For telephone interviews, interviewers will confirm before beginning the interview that participants can talk privately and safely. Interviewers will be trained to detect whether someone else is present or listening in on the call, using cues such as speech hesitations or background noises, and offer to call back if needed. If a participant is not alone, the interviewer will switch to asking nonsensitive, health-related questions as a safety measure. The online surveys will contain a preamble with online browsing safety tips, including specific recommendations to ensure the participant is alone before beginning the survey and instructions on how to use a private or incognito browser and how to quickly exit the survey. Furthermore, the WITHWomen Pathways app itself has safety features that participants can use should their abusive partner be made aware of their use of the app. As a mobile-friendly web app, WITHWomen Pathways is not physically downloaded, making it easier and quicker to remove any traces of its use. It also contains a quick exit button, which links to an innocuous website (currently hgtv.ca). In addition to these in-person and asynchronous safety measures, all participants completing the screenings by phone will be asked to confirm whether they feel that they are in a safe space, before moving forward. As rollout continues, the safety of completing interviews online will be considered and adjusted as necessary.

### Safely Contacting Participants

Safety protocols are of paramount importance in this study and necessitate bespoke approaches to safety strategies. To develop these strategies, we first consulted the literature and drafted a tentative protocol. These strategies include maintaining a general conversation during phone calls before discussing the research study until it is confirmed that the participant is in a safe environment, conducting regular check-ins to ensure the participant’s comfort and well-being, and sending an email prior to making phone calls to confirm that the scheduled time is still safe for the participant.

Our team’s peer advisory committee (comprising survivors and IPV advocates) provided feedback on the draft protocol and recommended changes to recruitment and contact procedures (eg, specifically mentioning IPV on recruitment flyers). During the consent process, participants will also be provided with an optional safe contact form where they can list up to 3 “safe contacts” who will only be contacted if the researcher cannot reach the participant. The purpose of this form will be communicated to participants as a standard procedure to ensure their safety if they cannot be reached. Safe contacts will be informed that the participant is part of a women’s health study and has given permission for the researcher to contact them if needed. Participants will be encouraged to inform their safe contacts about the possibility of being contacted by St Michael’s Hospital in the future. The participants will be asked to sign the safe contact form at baseline to ensure a thorough understanding and to provide written consent for contacting the listed individuals. Information requested for each safe contact includes name, relationship, phone number, and email. Participants will be asked to prioritize whom to contact first and to specify the preferred method of communication. The safe contact form will be reviewed and updated with participants at baseline and during follow-up to maintain accurate information.

### Follow-Up Communication Model

A communication protocol will be established between researchers and each participant, specifying when to expect contact from staff, ranking the preferred modes of safe contact (eg, email, phone, and mail), and choosing a code word to end communication if the environment is not private or safe. This information will be reviewed with participants at the first baseline and first follow-up assessments in case their situation changes. At each contact point, participants will be assured that their safety and confidentiality are prioritized and that the research team cares about them as individuals.

### Recruitment

While previous app-based safety planning interventions have attempted to reach women experiencing IPV who are unready to be connected with formal services [24], our community partners are interested in using WITHWomen Pathways as a complementary resource for those who present to formal services but are either unready (eg, ambivalent) or unable (eg, due to the presence of pets, male children, or substance use) to avail of temporary housing services or those who are unsure whether they need formal services. Therefore, participants will be recruited through a network of nearly 2 dozen organizations that provide violence against women services across the GTA. Prior to recruitment initiation, the research coordinator (SR) sent emails to staff at each organization about the purpose of this research and ensured that we were in agreement and alignment on participant safety and protocols for safety management, as well as the inclusion criteria. The organizational leadership has agreed to take part in the SCED evaluation study, allowing us to move forward with the recruitment process. To recruit participants, the research coordinator will share flyers and information sheets with the leadership, who will then share the materials with clients and others in their network via their own email listservs and social media accounts.

### Eligibility Screening and Informed Consent

Once a woman engages with recruitment material, the research coordinator will reach out using the participant’s preferred mode of contact (ie, email or phone) to invite her to learn more about the study and complete the eligibility screener. At the start of this discussion, participants will be provided with a “quick exit” strategy whereby the topic of conversation can quickly move to a safe subject in case privacy is breached. For example, study staff will inform potential participants that if either she or the interviewer notices that privacy is breached, they can quickly switch to talking about a “safe” topic of choice as determined by the participant (eg, shopping, cooking, children, sports, or movies).

The screener consists of questions about basic sociodemographic information (eg, age, residence, and sex), and the level of current or recent IPV is determined via the 9-item WITHWomen screener [39]. The target population for the SCED evaluation of the WITHWomen Pathways safety planning app is 6 self-identified women in the GTA who are currently experiencing physical, sexual, or emotional IPV or controlling behaviors or had these experiences in the past 12 months. Participants will be eligible if they are able to read, write, and speak English; identify as a woman; are 18 years or older; and reside in the GTA. Women who have custody of children younger than 13 years will also be eligible; this age was chosen to reduce the likelihood of multiple abusive partners (eg, presence of dating violence among adolescents) and better understand how women with young children make safety decisions. Men, individuals living outside the GTA, those with children older than 13 years, and those who are experiencing no IPV will be ineligible. Women who do not meet the eligibility criteria but who are experiencing IPV will be immediately referred to formal sources of support (eg, a domestic violence shelter, a hotline, or law enforcement). A separate safety protocol (available upon request) has been created, containing additional information on participant safety measures.

The eligibility screener can be completed in private interview rooms at study offices in downtown Toronto, using an online screener, or via telephone. For telephone-based screeners, the study staff will be instructed to keep the initial communication with potential participants as vague as possible until there is some assurance that they are in a private and safe location to hear more about the study.

Once a potential participant is deemed eligible to participate, the study staff will ask her whether she desires to continue to learn about the study and, if so, they will request her to provide informed consent to enroll. They will indicate that this process will take about 10 minutes. Informed consent can be provided immediately in person, via telephone, or via an electronic informed consent form. Staff can also arrange for a phone call at a later time to further discuss the study. The informed consent form outlines all study processes, including (1) study description, (2) a description of what is required of participants, (3) study duration, (4) expected time commitment from participants, (5) compensation, (6) data confidentiality, and (7) any potential risks or benefits of participation. Then, any questions the potential participant has will be answered by the study staff member (via telephone/in person). For electronic informed consent, contact information for the research coordinator and principal investigator will be provided in the event that participants have questions prior to providing their verbal consent or electronically signing the form. Participants will then be asked if they would like a copy of the form.

### Preintervention Assessments

As previously discussed, SCED requires the establishment of stability in a given outcome measure prior to intervention delivery [40]. We plan to assess 3 primary outcome measures that align with those assessed by previous RCT safety planning evaluations and are the direct targets of the intervention’s activities: safety self-efficacy, decisional conflict, and confidence in planning (see Table 1). These speak to the goals of safety planning, which are to *prime* those who are currently experiencing IPV to take action to improve their safety, which reflects the often nonlinear paths and ambivalence women feel about extricating themselves from a violent relationship [41,42]. Additionally, we plan to measure 2 secondary outcomes: IPV recurrence and mental health. IPV itself is a secondary outcome because changes in IPV exposure are not necessarily expected, for the reasons mentioned above. While mental health is not directly targeted by intervention activities in WITHWomen Pathways*,* participation in the intervention may secondarily lead to improvements in mental health through help-seeking actions.

**Table 1. T1:** Outcome variables for evaluation of *WITHWomen Pathways*.

Outcome measured	Primary/secondary	Instrument	Reference
Use and perceived helpfulness of safety strategies, service use	Primary	Intimate Partner Violence Strategies Index (adapted)	Goodman et al (2003) [43]
Empowerment related to safety	Primary	MOVERS^a^	Goodman et al (2014) [13]
Decisional conflict	Primary	Decisional Conflict Scale	O’Connor (1995) [12]
Anxiety and depression symptoms	Secondary	PHQ-4^b^	Kroenke et al (2009) [44]
Intimate partner violence	Secondary	Composite Abuse Scale-Short Form	Ford-Gilboe et al (2016) [45]

a MOVERS: Measure of Victim Empowerment Related to Safety.

b PHQ-4: Patient Health Questionnaire-4.

The baseline interview is designed to last approximately 15 to 20 minutes and will end with a reminder that the participant will complete some of these same measures every 3 to 4 days for the next 2 to 3 weeks until stability is reached. Participants will receive CAD $10 (US $7.15) as an online gift card or through electronic money transfer upon finishing each preintervention interview. Following the established safety protocols for working with those experiencing IPV described above, preintervention baseline assessments can occur via telephone, in person, or via an online survey, using the mode that seems the safest for the participant [46]. For telephone-based assessments, we will also ask the participant before beginning each session if she is in a private space. Whether collected remotely or in person, the SCED data will be recorded via Zoho Survey (Zoho Corporation) and saved directly to a secure Zoho server.

After each participant’s fifth baseline interview, the research team will assess the overall score for each outcome measure. If the participant achieves stability, measured using previously cited criteria wherein at least 85% of preintervention data fall within a 15% range of the median for at least 1 primary outcome measure (Patient Health Questionnaire-4 [PHQ-4], Measure of Victim Empowerment Related to Safety [MOVERS], and Decisional Conflict Scale), they will progress to the intervention interview [47,48]. If stability is not reached after 5 assessments, baseline measurements will continue for 2 more weeks (3 additional baseline measures with CAD $10 (US $7.15) compensation at each assessment) and reassessed. If, at this point, the participant’s outcome measures are deemed stable, they will proceed to the intervention interview. If not, they will still advance to the intervention visit, but their data will not be included in the effectiveness evaluation. Using the standard SCED protocol, these assessments will result in at least 5 but no more than 8 baseline measurements, ensuring that every participant receives the intervention as soon as possible [49].

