### Postintervention Interviews

Following standard SCED protocols, the postintervention assessments use the same questionnaires and intervals as the preintervention assessments [28]. At the first postintervention assessment (scheduled during the intervention interview), the participants will complete the same outcome measures at the same intervals (every 3‐4 days) as in the preintervention assessments. Participants with children will also complete the perceived child well-being questionnaire at the final visit. All participants will complete the same number of postintervention assessments (n=8) over the course of 4 weeks after their intervention interview. Postintervention interviews can be conducted in person, via telephone, or using the online survey.

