### Study Limitations

There are some notable limitations to this study. First, research activities require that women be able to speak and read English, which excludes non-English speakers and women with visual impairment. Second, with its multiple points of intervention and smaller sample size, SCED has safety and statistical limitations. First, having multiple contact points with each participant increases the chance that the abusive partner could become aware of her participation, increasing the risk of IPV. To address this, we have developed strict safety protocols and can promptly leverage our connections with local service providers should emergencies arise. SCED approaches also have multiple measurements in close temporal proximity, increasing participant burden. To help limit attrition, we will clearly communicate with potential participants about the time involved at the outset; invest in training for study team members to promote friendly, empathetic connection with participants; and provide fair compensation for the demands on participants’ time. Statistically, SCED carries four major risks: (1) the potential for a lack of variability in the preintervention and postintervention measures because measurements are completed at short intervals, (2) limited generalizability due to a small number of cases, (3) threats to internal validity due to test bias and social desirability bias [40], and (4) potential confounding effects due to the lack of randomization. To address risk 1, we will use the WWC recommendations for conducting sensitivity analyses and reporting multiple effect size estimators (eg, multiple visual analysis methods). Regarding risk 2, although multiple-case SCED (when rigorously evaluated) can be generalizable in many of the same ways as RCTs, this necessitates replication, which requires additional resources [57]. We do not anticipate this preliminary trial to be generalizable. Rather, it is intended to better identify the potential utility of SCED protocols in the evaluation of IPV-related interventions and adaptations that may be necessary. Regarding risk 3, we will use the percentage of nonoverlapping data, corrected (PNDC), to ascertain patterns of preintervention increase, as recommended by the WWC (see Table 2). Regarding risk 4, once this preliminary trial is complete, we intend to introduce randomization to different permutations of the WITHWomen Pathways app in future studies.

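### The reminder's baseline of 2 to 3 weeks leaves out the planned extension, whose spacing does not fit the 3-4 day interval, and its wording may reveal the rule that ends baseline

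*Protocol article*

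**What the plan says.** All but two of the relevant statements are in the Preintervention Assessments section of the protocol article.

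- **Reminder to the participant:** "the participant will complete some of these same measures every 3 to 4 days for the next 2 to 3 weeks until stability is reached".
- **First check:** "After each participant’s fifth baseline interview, the research team will assess the overall score for each outcome measure".
- **Criterion:** "at least 85% of preintervention data fall within a 15% range of the median for at least 1 primary outcome measure".
- **Extension:** "If stability is not reached after 5 assessments, baseline measurements will continue for 2 more weeks (3 additional baseline measures", each extra measure being compensated with CAD $10.
- **Bounds:** "these assessments will result in at least 5 but no more than 8 baseline measurements".
- **If stability is never reached:** "If not, they will still advance to the intervention visit, but their data will not be included in the effectiveness evaluation".

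Postintervention Interviews says that after the app visit women complete "the same outcome measures at the same intervals (every 3‐4 days) as in the preintervention assessments", with 8 assessments over 4 weeks. Eligibility Screening and Informed Consent says that the consent form covers study duration and expected time commitment. The wording of that form is not shown.

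**The concern.** Two stated figures disagree, and one phrase is risky.

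**Duration.** The reminder gives a length that the extension described in the next paragraph of the same section exceeds. A woman who is not stable at her fifth interview is followed for longer than she was told.

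**Spacing.** The design compares two phases that are said to be measured at equal intervals. The extension, as written, is slower than that interval.

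**Wording.** The outcomes are self-reports repeated every few days, and the Introduction says that the participant's own baseline serves as her control. Telling her that the phase continues until stability could hint that steady answers end it. Answers repeated for that reason would make the baseline look flatter than it is and easier to pass as stable. They could also reduce its overlap with later scores. Study Limitations already names test bias and social desirability bias as threats. The remedy it gives, the corrected percentage of nonoverlapping data, looks for a rise before the intervention. It is not aimed at a baseline that is artificially flat.

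**Working it through.** **Inputs** (Preintervention Assessments unless noted)

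- Interval between assessments: 3 to 4 days
- Announced duration: 2 to 3 weeks = 14 to 21 days
- First stability check: after 5 assessments
- Extension: 2 weeks = 14 days, with 3 measures
- Maximum: 8 assessments
- Postintervention Interviews: 8 assessments in 4 weeks, at the same 3-4 day interval

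**Step 1. Reproduce the announced duration.** The reminder looks forward from the first interview, so the span is (number of assessments − 1) × interval.

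- 5 assessments: 4 × 3 = 12 days to 4 × 4 = 16 days (1.7 to 2.3 weeks).
- Counting one full interval per assessment instead: 5 × 3 = 15 to 5 × 4 = 20 days (2.1 to 2.9 weeks).

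The announced 2 to 3 weeks is therefore a fair description of the unextended baseline.

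**Step 2. Add the extension as stated.**

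- 12 + 14 = 26 days to 16 + 14 = 30 days (3.7 to 4.3 weeks).
- Excess over the announced upper limit: 26 − 21 = 5 days to 30 − 21 = 9 days.

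The extended path passes 21 days at every permitted spacing.

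**Step 3. Alternative: all 8 assessments keep the 3-4 day interval.**

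- 7 × 3 = 21 days to 7 × 4 = 28 days (3.0 to 4.0 weeks).

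This stays within 3 weeks only if every gap is exactly 3 days. Counting one interval per assessment gives 8 × 3 = 24 to 8 × 4 = 32 days (3.4 to 4.6 weeks), which is over 3 weeks throughout.

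**Step 4. Spacing in the extension.**

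| Phase | Calculation | Days between measures |
|---|---|---|
| Stated interval | – | 3 to 4 |
| Extension | 14 / 3 | about 4.7 |
| Postintervention | 28 / 8 | 3.5 |

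At the stated interval, the three extra measures need 3 × 3 = 9 to 3 × 4 = 12 days. A full 2 weeks is 14 − 12 = 2 to 14 − 9 = 5 days longer than that.

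**Step 5. What the stability phrase can affect.** Set side by side, the provisions show that a woman who is stable at interview 5 goes to the app visit about 2 weeks earlier than one who is extended. Every woman receives the app after at most 8 baseline interviews. Stability therefore governs when she gets the app and whether her data enter the effectiveness evaluation, not whether she gets it.

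**The case against.** The strongest reply is that the sentence is the authors' short summary of a reminder, not the script. It may describe the usual course, with the tie to stability added for the journal reader. The consent form, which covers duration, may give the full range. Two weeks may be a rounding of 12 days, with some slack for scheduling. Tau-U compares all available pairs, so slightly wider gaps have no demonstrated effect on it.

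Much of this stands, and it keeps the point small. It does not remove the disagreement: whatever the consent form says, the article reports a reminder of 2 to 3 weeks and a schedule that runs past it. If two weeks is a rounding, the text still does not match the interval that it says both phases share.

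A reader might infer several stronger things that the documents do not support.

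- **That women are told consistent answers bring the app sooner.** Nothing says that participants learn what stability means, that it concerns their scores, or that it decides timing. The check is described as one made by the research team, and each extra interview is paid, so any incentive is mixed.
- **That the plan breaks its undertaking that "we will clearly communicate with potential participants about the time involved at the outset".** That undertaking concerns potential participants before enrolment. The reminder comes later, and the consent wording is not available to check.
- **That women may be followed up to 16 days longer than told (30 − 14).** This sets the longest path against the shortest announced one. The fair comparison is with the announced upper limit.
- **That a flatter baseline inflates the effect by a calculable amount.** Tau-U is not scaled by the baseline SD, so an argument in SD units does not carry over to it.
- **That the understated duration will cause dropout.** Nothing in the article links the two.

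**Conclusion.** The concern holds in a limited form. The announced baseline duration is wrong for any woman who is extended: 26-30 days against an upper limit of 21, an excess of 5-9 days and three further interviews. The extension's spacing of about 4.7 days conflicts with the 3-4 day interval claimed for both phases. These results rest on reading the extension as a full 14 days after the fifth interview and on counting from the first interview. If all 8 assessments instead keep the 3-4 day interval, the maximum is 21-28 days, which exceeds 3 weeks unless every gap is 3 days.

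The disclosure of the rule that ends baseline is a possibility, conditional on the words being spoken as written and understood. Its effect on the results cannot be sized from the article, and neither can the share of women who will be extended. The whole point is of low severity, but the text needs correcting.

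**What to change.** 1. Have the reminder state 5 to 8 interviews over about 2 to just over 4 weeks before the app visit. The upper figure should follow from whatever is settled under item 4.
2. Check that the consent form and consent discussion give the same range.
3. Leave the stability condition out of what participants are told. If the phrase is only the authors' gloss and is not spoken, say so.
4. Reconcile the two-week, three-measure extension with the 3-4 day interval, so that the statement about equal intervals in both phases is true as written.

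The cost is wording only, and the stated time commitment will look slightly longer at enrolment. Results says that four of the planned six women have completed the study and that recruitment continues, so the new wording can still reach the remaining participants.

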### Strategies to Prevent Attrition

Given the high participant burden of SCED and the potentially precarious position in which many women experiencing IPV find themselves, attrition from the study is likely. However, the research team has devised strategies to safely encourage participants to remain in the study. First, the study is designed to be as convenient for participants as possible, offering several modes of contact (in person, via telephone, and online), evening and weekend assessment options, and face-to-face interviews at partner organizations convenient to the participant. Compensation will also be given at the point of assessment, within a day following each check-in, and each assessment will be scheduled at the end of the preceding visit. For those who do not attend previously scheduled assessment visits, researchers will first reach out via the safe contact methods indicated by the participant at different times of the day. They will then search for updated information or attempt previously disconnected phone numbers before reaching out to the safe contacts listed by the participant. While resource limitations prevent us from overenrolling to guard against attrition, sample size is only one of several levers that SCED studies (as opposed to traditional evaluation designs) can use to improve statistical power. Should attrition become an issue, we will explore using additional baseline and follow-up measures in the remaining participants, simulating power using different effect size estimates, and assessing the number of outlier scores to understand its effect on generalizability [50].

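### Baseline payments are named only in electronic forms and are not stated to follow each woman's safe-contact plan, so a woman without a safe inbox or account has no named safe route

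*Protocol article*

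**What the plan says.** All references are to the protocol article.

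- **Form of payment (Preintervention Assessments):** "Participants will receive CAD $10 (US $7.15) as an online gift card or through electronic money transfer upon finishing each preintervention interview". If stability is not reached after five assessments, there are "3 additional baseline measures with CAD $10 (US $7.15) compensation at each assessment"; the form is not repeated there.
- **Timing of payment (Strategies to Prevent Attrition):** "Compensation will also be given at the point of assessment, within a day following each check-in". This covers check-ins generally and is presented as a retention measure. It gives no form.
- **Postintervention Interviews and Intervention Interview:** neither section states an amount or a form of payment.
- **Assessment mode (Preintervention Assessments):** telephone, in person or online, according to what appears safest for the woman.
- **Contact plan (Follow-Up Communication Model):** agreed with each woman, covering when staff will make contact, a code word, and "ranking the preferred modes of safe contact (eg, email, phone, and mail". Payment is not mentioned.
- **Other safeguards (Universal Safety Considerations, Safely Contacting Participants):** private browsing advice, a quick exit button, an app that is not downloaded so that its traces are easier to clear, and an email before each call. Payment is not mentioned here either.
- **Risk (Study Limitations):** having several contact points "increases the chance that the abusive partner could become aware of her participation".
- **Documents not shown:** Eligibility Screening and Informed Consent refers to a separate safety protocol, available on request, and says that the consent form covers compensation and risks.

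**The concern.** The article adapts contact to each woman's circumstances but restricts payment to two electronic routes. A woman might choose in-person interviews precisely because her phone, inbox or bank account is watched. As written, she would still receive a gift-card message or a transfer entry after every baseline interview. That is the sort of recurring electronic trace that the app and survey safeguards are designed to avoid, and the eligible population includes women currently living with controlling behaviours.

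What is at stake is participant safety and, through it, the study's first objective: whether women can be safely followed up intensively, measured by a lack of reportable or adverse events. No estimand, analysis or sample-size figure is affected, except possibly through attrition if a woman drops out because payment feels unsafe.

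**Working it through.** The article gives no total number of payments, so there is no figure to reproduce. The check counts paid contacts from the stated schedule and then sets the payment rule beside the contact rules.

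**Inputs**
- Baseline assessments: "at least 5 but no more than 8 baseline measurements".
- Interval: "every 3 to 4 days for the next 2 to 3 weeks until stability is reached". The extension is 3 more assessments in 2 weeks.
- Postintervention: "All participants will complete the same number of postintervention assessments (n=8) over the course of 4 weeks after their intervention interview".
- Payment: CAD $10 per baseline assessment.

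**Payments with a documented electronic form (baseline)**
- Number: 5 to 8 per woman.
- Value: 5 × 10 = CAD $50, to 8 × 10 = CAD $80.
- Spacing of the first five: 3 to 4 days. Four intervals span 4 × 3 = 12 to 4 × 4 = 16 days.
- Spacing of the three extra: 14 / 3 ≈ 4.7 days.
- Overall, a payment about every 3 to 5 days. The form is stated for every preintervention interview, so I count the extension assessments too.

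**Payments if the postintervention assessments use the same form (assumption)**
- Number: 5 + 8 = 13, to 8 + 8 = 16.
- Postintervention spacing: 28 / 8 = 3.5 days.
- Period: 12 + 28 = 40 days at the shortest. At the longest, (16 + 14) + 28 = 58 days. Any gap around the intervention visit is not counted.
- If the intervention visit were also paid this way: 14 to 17.

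**Rules side by side**

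| Aspect | Contact and assessment | Payment |
|---|---|---|
| Form | In person, telephone or online for assessments; email, phone or mail given as examples for contact | Online gift card or electronic transfer (baseline); not stated afterwards |
| Chosen for the woman's safety? | Yes, in her individual plan | Not stated |
| Timing | Agreed with her | On finishing each baseline interview; elsewhere, within a day of each check-in |
| Reviewed if her situation changes? | Yes, at first baseline and first follow-up | Not stated |

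The two timing statements, on finishing and within a day, also differ slightly and should be aligned.

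**The case against.** The strongest reply is that this is largely an inference from silence in a condensed article. Emailing a gift card is itself a contact by staff, and nothing exempts it from the agreed plan. Email is one of the modes a woman may rank as safe, and a gift card sent to that address may add little to the emails and online surveys already in use. The separate safety protocol and the consent form are not shown and may deal with payment. Prompt payment is a deliberate retention measure. Non-electronic payment would require attendance, and one larger held payment could be more conspicuous than CAD $10.

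Much of this stands, and it rules out three stronger readings that a reader might infer:

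- *That every contact is paid electronically.* The form is stated for preintervention interviews only. The attrition section shows that later check-ins are compensated, but not how.
- *That payment lies outside the safe-contact rules.* The article says only that the plan covers contact. It neither includes nor excludes payment.
- *That the protocol names payment as a discovery risk, or discovery as its main hazard.* The limitations section ties the risk to repeated contact and does not rank it. That payments add to the risk is plausible, but no figure supports it.

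The reply does not remove the point. The restriction to two electronic forms is a stated rule, not an omission. A safe email address helps only a woman who has one. If the safety protocol does allow other forms, the baseline payment rule does not reflect that and the two need aligning. Disclosing compensation at consent does not in itself give a choice of form.

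**Conclusion.** The point holds for the baseline phase. The article names only electronic payment there, 5 to 8 times per woman at intervals of about 3 to 5 days, and does not say that form or timing follows her individual communication plan. A woman without a safe inbox or account has no named safe route. The 13 to 16 total is conditional on the postintervention assessments being paid the same way.

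This is a low-cost safety improvement to a stated rule, not a demonstrated failure of the safety procedures. The added discovery risk cannot be quantified from the article. Its reach in this study is small: the Results report 4 participants as having completed, against a target of 6, which leaves 6 − 4 = 2 places. Recruitment is still under way, however, and further single-case evaluations are planned.

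**What to change.** Add payment form and timing to the individual plan in the Follow-Up Communication Model. At consent each woman would choose between:

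- electronic payment to an address or account that she has agreed is safe;
- a non-electronic form handed over at an in-person contact or a partner agency; or
- payments held and made together.

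Review the choice whenever her contact modes are reviewed. State the form of payment for the postintervention assessments, use one statement of timing throughout, and bring the Preintervention Assessments section and the separate safety protocol into line with the plan.

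**Cost:** a short addition to the text and minor administration. The other downsides fall only on women who choose the alternatives: held payments weaken the immediate incentive and produce a larger, possibly more conspicuous, single payment, and non-electronic payment requires attending in person. Women content with the present routes would see no change.
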